### Sample size

2.5

Previous single-armed trials investigating (manual) tactile training for patients with chronic pain found moderate to large effect sizes for within group change in tactile acuity (26% improvement, mean change: TPDT 17.1 mm, p < 0.01, Cohen's d = 1.06) [28] and pain intensity (22% improvement, mean change: VAS 1.0 cm, p = 0.02, Cohen's d = 0.55) [16]. We therefore expect that we need to reach at least medium-large effects in tactile acuity in order to mediate clinically meaningful changes in pain. However, these effect sizes are based on within-group change since a control group was not present. Nevertheless, similar size differences in change of pain intensity have been reported when comparing tactile acuity training to a control condition for: neck pain [29] (24% difference, Δ NRS 1.6 points, p = 0.02, Cohen's d = 0.44); back pain [29] (41% difference, mean change: NRS 2.3 points, p < 0.01, Cohen's d = 1.07); and phantom limb pain [30] (45% improvement, mean change: Multidimensional Pain Inventory 1.5 points, p = 0.02, Cohen's d = 1.16). However, since these studies did not include tactile acuity as an outcome measure, they are not directly informative for our primary research question. As such, a sample size calculation was performed to account for a >90% chance of finding a statistically significant (p < 0.05), medium-large ($\eta_{p}^{2}$ = 0.1) between-group difference in tactile acuity, using a within-between repeated-measures ANOVA with four time-points. The calculation estimated that 18 participants would be required. Accounting for a dropout rate which can be up to 20% for treatments involving active participation in people with health conditions [31,32] a pool of 24 participants (12 in each arm) were estimated to be necessary. To improve power to explore secondary outcomes, particularly within the tactile training group, the target sample size for the intervention arm was doubled (n = 24 intervention group; n = 12 control group).

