***Feasibility:*** Feasibility, with respect to planning a full-scale RCT, will be assessed according to recommended a framework [34]. Data to assess feasibility will be extracted from a digital record of recruitment and screening-related interactions, iTAD digital usage logs, participant completion rates, and questionnaires related to blinding, treatment credibility, and treatment satisfaction. For the protocol to be classified as feasible, a priori cut offs have been determined. These include: 1. A minimum intake of two participants per week and a positive recruitment rate of at least one participant intake out of every four invited, 2. An 80% treatment completion rate, 3. A follow-up rate of 70%, 4. A maximum of 10% missing data for primary and secondary outcomes for those that completed the study, 5. Adherence rates where at least two-thirds of participants complete over 50% of the prescribed training, 6. No statistically significant difference in credibility between intervention and control, a 7. Bangs blinding index of 0 ± 0.2 for both treatment arms as well as the outcome assessor (on a −1 to 1 scale, where scores closer to 0 represents being more unsure of group) [[35], [36], [37]], and 8. Neutral positive satisfaction with treatment ratings for both treatment arms.

***Adverse events:*** For the purpose of this trial, a serious adverse event is defined as an unwanted and harmful outcome that: 1. be related to the intervention, and 2. is significant enough to require medical attention. A minor adverse event will be defined as any unwanted outcome that: 1. either interferes with activities of daily living or persists for more for 24 h, and 2. can be related to the intervention. Adverse events will be monitored during the weekly phone calls with the study clinician.

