### Data analysis

2.13

The effect of training on tactile acuity will be assessed using a mixed-design two-way analysis of variance (ANOVA) with one between group factor with two levels (Group: iTAD and iTENS) and one repeated factor with four levels (Time: baseline, mid-treatment, 5-week and 2-month outcome assessment). While pain intensity and spread, disability and iTAD scores will be analysed with the same mixed-design AVOVA, the focus of interpretation will be to inform future sample size calculations, and selection of primary outcomes for future trials. For GPE scores, the percentage of people reaching our criterion for improvement (≥+3) will be calculated for each group for descriptive analysis. A multiple linear regression approach will be used to observe whether change in tactile acuity in the iTAD group is predicted by time spent training, baseline tactile acuity scores, baseline sleep (Insomnia Severity Index) and psychological status (Depression Anxiety Stress Scale). Where appropriate, results will be expressed in terms of statistical significance, effect size, descriptive statistics, and plots. Should the final data set contain >5% missing data for the primary outcome, a multiple imputation method will be used to replace missing values [43]. Rates of usual care modalities will be compared between groups in order to identify and discuss their possible influence.

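### The 5% imputation trigger, with its unit undefined, can leave up to 7 of 36 participants out of a mixed ANOVA that needs all four visits, with nothing imputed

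*Protocol article*

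**What the plan says.** Section 2.13 (Data analysis) of the protocol article fixes the primary model as a "mixed-design two-way analysis of variance (ANOVA) with one between group factor with two levels" and "one repeated factor with four levels (Time: baseline, mid-treatment, 5-week and 2-month outcome assessment". For missing data it gives one rule: "Should the final data set contain >5% missing data for the primary outcome, a multiple imputation method will be used".

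The article then says that "pain intensity and spread, disability and iTAD scores will be analysed with the same mixed-design AVOVA", with interpretation aimed at planning future trials. Table 1 schedules tactile acuity, pain, spread, disability and iTAD scores at the same four visits.

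Section 2.5 allows for dropout of up to 20% and sets the final target: "the target sample size for the intervention arm was doubled (n = 24 intervention group; n = 12 control group". Section 2.10 lists feasibility cut-offs that include 70% follow-up and, among those who complete the study, at most 10% missing data for primary and secondary outcomes.

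**The concern.** The model and the rule do not fit together. A classical mixed-design ANOVA needs a complete row of four measurements per participant. That is a property of the method; the article does not state it. At or below the trigger nothing is imputed, so a participant who misses one visit loses the three values that were observed. Above the trigger the approach changes to imputation. Because the 5% has no stated unit, the same data set can fall on either side of the line.

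The trigger also looks only at the primary outcome. The same ANOVA is applied to pain, spread and disability, but gaps in those measures alone can never activate imputation.

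What is at stake is mainly bias. One arm plays training games on a tablet at home; the other uses a de-activated unit for a matched time. The Introduction itself names the engagement required as a possible barrier to recruitment and retention. If loss differs by arm or by response, a comparison restricted to complete rows is no longer the randomised comparison. The same selection would affect the pain estimates meant to inform future sample sizes.

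**Working it through.** **Inputs.** From section 2.5: 36 randomised (24 + 12), planned dropout up to 20%, partial eta squared 0.1, alpha 0.05, power above 90%, 18 participants before dropout and 24 after. From section 2.13: four time points and the 5% trigger. Assumed because the article does not state them: correlation between visits 0.5 and no sphericity correction.

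**1. The plan's own sample size.** For the group x time interaction, f² = 0.1/0.9 = 0.111 and lambda = f² x N x 4/(1 - 0.5). With N = 18, lambda = 0.111 x 18 x 4/0.5 = 16.0, on 3 and (18 - 2) x 3 = 48 degrees of freedom. Power is 0.912, and 18 is the smallest N that reaches 90%. Dropout: 18/0.8 = 22.5, so 23, or 24 for equal arms. The stated figures reproduce under these assumptions.

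**2. How many can be lost without imputation.** Take the largest count not exceeding 5%, with each affected participant missing exactly one visit.

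| Unit of the 5% | Total | 5% of total | Largest count at or below 5% | Participants dropped |
|---|---|---|---|---|
| All values of one measure | 36 x 4 = 144 | 7.2 | 7 (7/144 = 4.86%) | 7/36 = 19.4% |
| Post-baseline values of one measure | 36 x 3 = 108 | 5.4 | 5 (5/108 = 4.63%) | 5/36 = 13.9% |
| Participants | 36 | 1.8 | 1 | 1/36 = 2.8% |

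An eighth participant missing one visit gives 8/144 = 5.56% and triggers imputation.

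**3. How far the upper bound depends on the pattern** (all 144 values counted). If each affected participant misses two visits, at most 3 (8.3%) are dropped before the trigger fires; if three visits, at most 2 (5.6%).

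**4. Against the planned dropout.** 20% of 36 is 7.2, so about 7 people. If all seven miss only the last visit, 4.86% of values are missing and nothing is imputed. If each misses two visits, 14/144 = 9.7% are missing; if three, 21/144 = 14.6%. Both trigger the rule.

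**5. Against the 70% follow-up cut-off.** 30% of 36 is 10.8, so about 11 people. Even if all miss only the last visit, 11/144 = 7.6%, and the rule is triggered.

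**6. Effect on power.** Using 4 x n1 x n2/(n1 + n2) as an approximate effective N in the formula of step 1:

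| Analysed (iTAD + iTENS) | Effective N | Power |
|---|---|---|
| 24 + 12 | 32.0 | 0.996 |
| 19 + 10 | 26.2 | 0.985 |
| 17 + 12 (all seven lost from iTAD) | 28.1 | 0.991 |
| 24 + 5 (all seven lost from iTENS) | 16.6 | 0.883 |

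Only the extreme case of all seven lost from the control arm falls below 90%.

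**The case against.** Several points on the other side have force.

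- **A condensed article.** The unit of the 5% and the scope of imputation could be defined in a full protocol or analysis plan that is not shown. Silence on these would not be a finding by itself. What stands is that the article fixes a complete-row model and an imputation threshold together, and under each of the three units in the table at least one participant can be dropped without imputation.
- **19.4% is a corner case.** It needs a per-value count that includes baseline and exactly one missed visit for each of seven people. This is correct, so it can be stated only as an upper bound.
- **The rule is pre-specified.** It responds to the amount of missing data, not to the observed treatment effect. That is also correct. It remains open to a choice of unit once the extent of missing data is known.
- **Power is barely affected** in most patterns, as step 6 shows. This stands, and the case rests on bias and discarded data.
- **Limited consequence.** Section 2.13 confines pain and disability to planning, section 3.2 disclaims conclusions on secondary outcomes, and Table 1 classes disability as exploratory. This lowers the stakes for those outcomes but not for tactile acuity.

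A reader might infer that pain and disability will be analysed in completers only, however high the dropout. The article does not say so. The primary outcome sets the trigger, but the sentence does not limit imputation to primary values. The outcomes share visits, so heavier dropout would set the rule off (step 5). Nor would the loss be hidden: dropouts, follow-up and missing data are feasibility outcomes with numeric cut-offs. The 70% cut-off is a criterion for judging feasibility, not a statement of how much loss the analysis may tolerate.

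**Conclusion.** The concern holds in a bounded form. As written, section 2.13 can exclude up to 7 of 36 participants (19.4%) from the analysis of a primary measure with no imputation if the 5% counts all values, up to 5 (13.9%) if it counts post-baseline values, and 1 (2.8%) if it counts participants. These figures assume a classical ANOVA that deletes incomplete rows and one missed visit per affected participant; longer absences lower the first figure to 8.3% or 5.6%. Missing pain, spread or disability data cannot trigger the rule alone, and whether imputation reaches them once triggered is left open.

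The weight of the point is possible bias from arm-related loss and the waste of observed data. That loss will differ by arm is plausible from the design, but the article gives no figures to show it. The point should be corrected before analysis; it does not undermine the sample size.

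**What to change.** Delete the 5% trigger. Analyse the primary and secondary continuous outcomes, and disability (which section 2.13 puts through the same ANOVA), with a linear mixed model fitted by restricted maximum likelihood to all available visits of every randomised participant, whatever the amount of missing data.

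State how baseline enters. Either keep it as a level of Time, as now planned, with the group x time terms carrying the treatment comparison, or enter it as a covariate with the three post-baseline visits as the response. In the second form a participant with no post-baseline visit contributes nothing; this should be said and such participants counted by arm.

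State that the model assumes data missing at random. Keep multiple imputation as a sensitivity analysis for the primary outcome, and say whether it also covers pain, spread and disability.

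The cost is analysis-plan wording and slightly more analysis work in standard software, with no new data. The model relies on missing at random, so it does not cure dropout driven by unobserved response. That is still a weaker assumption than the complete-case ANOVA needs.

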### Data management and fidelity to protocol

2.14

Participants will be given a unique code at the beginning of the study that will be linked to their personal details (name, contact information, group allocation) via an encrypted digital file. Data will be stored on the research data management cloud platform ResearchSpace using a personal institutional login accessible only by the researchers. Participant information and data will never appear with their name, date of birth, or contact details. In this way, their data are only re-identifiable by the researcher. No identifiable, or re-identifiable, information will be included in notes or publications. Given the short, low-risk, nature of the trial, no independent Data Monitoring Committee is required [44]. Trial conduct will be monitored by members of the team through peer observation of fidelity to protocol, and by peer auditing of data files for entry and transcription errors. Any amendments to the protocol will be submitted to the ethics review board, the Australian New Zealand Clinical Trial Registry, and will be reported in the trial manuscript.

### Patient and public involvement

2.15

Interviews of people with neck pain attending cross-sectional studies involving the device have been key informants for identifying areas for improvement including: 1. The comfort of the device, 2. The usability of tablet computer user interface, 3. Treatment appeal and likelihood of trial participation, and 4. Instructions for participants. People with neck pain were also consulted regarding the design of the iTENS control condition, and the treatment explanations, and their feedback led to modifications in the language used to ensure its perceived credibility.

## Discussion

3

### Potential impact and significance

3.1

Persistent pain conditions represent a massive personal and societal burden [45] Adaptations in the nervous system play a role in many persistent pain states and developing interventions that to target these factors is of high importance [46]. Deficits in tactile acuity demonstrated in people with neck pain and other conditions are likely to reflect a specific type of underlying nervous system adaptation to pain and/or injury [1,2,[47], [48], [49]]. This trial represents an investigation of one of the few treatments specifically designed with these nervous system adaptations in mind. While proposals that training tactile acuity might reduce pain are not new, it has not been widely used in clinical practice because of the time and human resources required to deliver it. The iTAD device has the potential to overcome this barrier, by enabling independent in-home use. This randomised controlled pilot trial is a first step towards establishing whether training with the iTAD can improve tactile acuity and ameliorate symptoms.

### Strengths and weaknesses of the study

3.2

A strength of the study is the use of participants attending secondary care, a population that may be more likely to present with a significant central nervous system adaptation as a contributor to their symptoms. Further, we have implemented tools to assist in controlling for non-specific effects and bias such as a placebo intervention and blinded assessors. Weaknesses of the study include its inability to blind the therapist and inability to draw conclusions on secondary outcomes due to the low participant numbers in this proof-of-concept study. However, results relating to secondary and exploratory outcomes will assist to inform larger scale studies aiming to determine whether tactile training can improve outcomes such as pain.

## Conclusion

4

If the current study shows improvement in tactile acuity relative to control, and if secondary data support the possibility of pain reduction, then there are significant potential benefits of continuing iTAD development and research. These include the prospect of a practical method of training tactile acuity and progress towards effective treatments for persistent pain. The trial results will be disseminated via publication in academic journals and presentation at academic conferences.

## Ethics approval

The study is approved by the Human Research Ethics Committee of Griffith University (2017/128).

## Clinical trial registration

The study is registered with the Australia and New Zealand Clinical Trials Register (ACTRN12621000615886). UTN: U1111-1252-9527.
